## Abstract

**Background:**

South Korea is anticipated to enter a super-aged society by 2025, necessitating a focus on healthy aging. In Korean medicine (KM), aging and disease susceptibility are individual specific, emphasizing personalized treatments, and many Korean local governments have integrated KM services for elderly people into the public sector. However, there is a notable absence of research incorporating KM to treat older adults.

**Aim:**

The proposed study aims to examine the comprehensive health profiles of individuals entering old age in rural and urban areas and explore the significant correlations between healthy aging and four key factors: biological, psychological, social, and KM-based phenotype factors. It will also establish a database and blood biobank, serving as a platform for future research to develop a traditional KM-based healthy aging model.

**Methods:**

A multiple randomized controlled trial design will be adopted in this prospective, multicenter cohort study for the clinical investigation of the markers associated with KM-based healthy aging. The aim is to recruit 1,000 participants who are entering old age from both urban and rural settings for this study, and recruitment began in August 2023 with follow-up surveys planned at one-year intervals. Comprehensive health profiles, including biological, psychological, social, and KM-based phenotype factors, will be developed through the creation of a database, a blood biobank, and multi-omics data.

**Results:**

In the baseline phase of this study, we will focus on identifying markers for KM-based phenotypes and examining how these phenotypes relate to aging and associated diseases. In the next phase, we will implement interventions tailored to KM-based phenotypes to verify the effects of KM on healthy aging. Ultimately, we intend to develop a KM-based integrated health management model, with further substudies aiming to explore factors related to healthy aging. This protocol was approved by the institutional review board of Wonkwang University Korean Medicine Hospital, Iksan, Republic of Korea (approval number: WKUIOMH-IRB-2023-05) on August 16, 2023 and Jangheung Integrative Medical Hospital (approval number: WKUJIM-202307-001) on August 21, 2023. Recruitment started on August 16, 2023.

**Conclusion:**

The anticipated results of our study aim to establish personalized preventive and therapeutic interventions for individuals entering old age. Additionally, we seek to offer an KM-based integrated health management model that incorporates comprehensive diagnosis and an integrative medical treatment strategy for healthy aging.

**Trial Registration:**

Clinical Research Information Service: KCT0008863 (registered on October 11, 2023, https://cris.nih.go.kr/cris/search/detailSearch.do/25718).

## Introduction

According to Statistics Korea, South Korea is anticipated to transition into a super-aged society by 2025, just seven years after entering an aged society in 2018. By the year 2060, it is estimated that 43.9% of the population will be classified as elderly [1]. As the super-aged era approaches, there is a growing societal emphasis on enhancing quality of life and placing greater attention on promoting healthy aging to ensure that individuals age while maintaining a state of well-being [2].

The World Health Organization (WHO) defines healthy aging as a holistic approach that prioritizes intrinsic capacity, functional ability, and well-being, with an emphasis on an inclusive environment, integrated care, community support, and chronic disease management for a positive aging experience [2,3]. With the increasing interest and demand for healthy aging, the focus has been on improving quality of life through integrative medical treatments through multidisciplinary diagnoses and preventive screenings, as opposed to simple therapies [4,5].

As part of these initiatives, various studies are underway to propose strategies for healthy aging [5]. Notably, significant studies, including the Korean Longitudinal Study of Aging, have focused on aging and the quality of life of elderly individuals in South Korea [6]. Additionally, a Korean frailty and aging cohort study concentrated on physical health and chronic conditions among Korean seniors [7]. Moreover, the Korean Brain Aging Study for Early Diagnosis and Prediction of Alzheimer’s Disease was conducted, focusing on brain cognitive functions, aging, and Alzheimer’s disease [8]. Despite numerous cohort studies targeting Koreans, these efforts have yet to incorporate assessment criteria related to traditional Korean medicine (KM). Additionally, there is a notable absence of cohort studies presenting health management methods that incorporate the concepts of traditional KM in the context of healthy aging among elderly people [9].

In particular, in KM, the aging process and susceptibility to disease vary according to an individual’s phenotype, and KM emphasizes personalized treatments and preventive measures tailored to an individual’s unique characteristics [10]. Thus, KM continues to be widely utilized among many Koreans, coexisting seamlessly with Western medicine. Additionally, the Korean government has incorporated KM services for elderly individuals into the public sector, and 242 local governments (46.5% of localities) provide public TKM services [11]. This underscores the need for studies within cohorts that include KM. In addition, South Korea experiences differences in the living environments of elderly people in rural and urban areas, as well as variations in community cohesion and health behaviors among residents. Many studies have compared these characteristics and investigated life satisfaction [12–14]. Therefore, in the context of South Korea’s elderly cohort studies, there is a need for research that not only targets the general population but also considers the regional characteristics of the participants.

In this study, we aim to examine the comprehensive health profiles of individuals entering old age in rural and urban areas and explore the significant correlations between healthy aging and four key factors: biological, psychological, social, and KM-based phenotype factors. Additionally, we will establish a database and blood biobank. Furthermore, this study will serve as a recruitment platform for future intervention studies using a cohort multiple randomized controlled trial design [15], contributing to the development of a health management model for promoting healthy aging based on traditional KM. Ultimately, we intend to develop a traditional KM-based healthy aging model, with further substudies aiming to explore factors related to healthy aging based on KM-based phenotypes.

## Methods

### Study design

This will be a prospective, multicenter cohort study that adopts a multiple randomized controlled trial design [15] to clinically investigate markers associated with KM-based healthy aging. The baseline phase is scheduled from August 2023 to December 2024, aiming to recruit 1,000 participants. Each participant will undergo two follow-up assessments, the first occurring one year post-enrollment, extending the study period through 2025 (Fig 1).

**Fig 1 pone.0316986.g001:**
[figure not shown]
Schedule of assessments and procedures for aging cohort (KoMAC) study. Screening: Initial assessment phase before baseline visit, including consent and eligibility checks. Visit 1 (Baseline): Baseline data collection, including demographic survey, physical measurements, health habits, and initial health assessments. Visit 2 (1-year follow-up ±  4 weeks): Follow-up assessments conducted 1 year after baseline to monitor health changes, excluding clinical lab tests. Visit 3 (2-year follow-up ±  4 weeks): Final follow-up assessments conducted 2 years after baseline, similar in scope to Visit 2.

### Study sample

This study will be conducted with a target group of 1000 participants who are entering old age and who are recruited from Wonkwang University Korean Medicine Hospital, a medium-sized city, and Jangheung Integrative Medical Hospital, a rural area in South Korea. The objective is to investigate potential cohort losses due to yearly mortality and other factors, with a target panel retention rate exceeding 80%. Despite limitations in achieving perfect representativeness of the population, practical feasibility will be considered by selecting research participants based on the demographic distribution of the population aged 50–65 years in Iksan and Jangheung, Jeonbuk, as of 2023 [16,17]. Considering the budget for this cohort project and the target population of individuals entering old age at Iksan and Jangheung in 2023 (for a total of 82,498 individuals), the goal is to recruit approximately 1% of this target population while factoring in a panel dropout rate of 20%. Therefore, the aim is to register a total of 1,000 adult participants, encompassing both sexes.

### Study population

This study will be This proposal involves recruiting 1,000 individuals over a two-year period from August 2023 to December 2024 for the study of individuals entering old age. Eligible participants will be identified by Clinical Research Coordinators (CRCs) from each institution who receive thorough training regarding the inclusion/exclusion criteria and recruitment procedures.

The inclusion criteria are as follows: (1) adults aged 50 to 65 years; (2) adults residing in either a medium-sized city (Iksan city and nearby areas in Jeonbuk state) or a rural area (Jangheung County and nearby areas in Jeonnam state); (3) adults who can read and respond to the questionnaire; and (4) adults who understand the purpose of the study and provide written consent to participate. The exclusion criteria are as follows: (1) a history of major psychiatric disorders diagnosed by the DSM-5, such as psychotic symptoms, schizophrenia spectrum disorders, delusional disorders, bipolar disorders, alcohol or substance use disorders; (2) the inability to communicate effectively or limitations in reading and writing; and (3) determination by the research team or responsible personnel that the study cannot be completed due to a medical condition. Additionally, (1) participants for whom the selected or excluded criteria are violated following screening, (2) participants who withdraw consent during the study, and (3) participants who are not traceable will be considered premature withdrawals from this study.

After registration, follow-up examinations will be performed at 1-year intervals from August 2024 to December 2025. However, blood tests will be administered every two years: at baseline and during the final follow-up. A strategy for sustained participation will be adopted to keep participants engaged in the cohort study. This will include sending quarterly health management information through a webzine and providing free health consultation services to prevent dropout of participants. Additionally, substantial compensation will be provided every visit, along with immediate explanations of the health screening process, to minimize participant attrition.

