### Study procedures

After commencing the research, banners for participant recruitment will be displayed in local public health care institutions and health centers. Contact will be initiated with individuals who respond to the banners; their age will be verified and visit schedules will be coordinated. Participants will be asked to maintain fasting for eight hours before their scheduled institution visit and to bring photographs of any nutritional supplements or medications that they are currently taking.

At the first visit, a research nurse will provide an overall explanation of the study. Then, the specific tests scheduled for the day will be detailed using a worksheet, with the nurse providing thorough explanations and addressing any queries immediately. After completing the explanations, participants will sign the research consent form and the consent form for the use of human-derived materials.

A medical registration form will be provided only to participants who sign both forms. For fasting patients, blood tests will be conducted first, and a light snack will be provided for those who complete the blood draw. Subsequently, participants will complete the all surveys and examinations. The entire examination process will take approximately 1 hour and 30 minutes. Upon completion, participants will be provided with information regarding their next examination date. Recruitment began on August 16, 2023, at Wonkwang University Korean Medicine Hospital and on August 22, 2023, at Jangheung Integrative Medical Hospital. It is expected to be completed by December 31, 2025.

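### The stated dates cannot all hold: follow-up to December 2025 fits the one-year visit only, so nobody enrolled after 28 January 2024 could have Visit 3 or the second blood sample

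*Protocol article*

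**What the plan says.** All statements are in the Methods of the protocol article.

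- **Enrolment.** Study design: "The baseline phase is scheduled from August 2023 to December 2024, aiming to recruit 1,000 participants". Study population repeats the dates but describes them as "recruiting 1,000 individuals over a two-year period from August 2023 to December 2024". Study procedures gives the actual start: "Recruitment began on August 16, 2023, at Wonkwang University Korean Medicine Hospital and on August 22, 2023, at Jangheung Integrative Medical Hospital".
- **Visits per participant.** Study design: "Each participant will undergo two follow-up assessments, the first occurring one year post-enrollment, extending the study period through 2025".
- **Timing of Visit 3.** The Fig 1 caption labels it a 2-year follow-up with a window of 4 weeks either side: "Final follow-up assessments conducted 2 years after baseline, similar in scope to Visit 2".
- **Second blood sample.** Study population: "blood tests will be administered every two years: at baseline and during the final follow-up". In Table 1 the clinical laboratory row, which includes the metabolomics/lipidomics and proteomics, is marked for Visits 1 and 3 only.
- **End of follow-up.** Study population: "follow-up examinations will be performed at 1-year intervals from August 2024 to December 2025".
- **Completion.** Study procedures, directly after the recruitment start dates: "It is expected to be completed by December 31, 2025".

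No section extends follow-up into 2026.

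**The concern.** A participant enrolled at the end of December 2024 reaches the two-year visit at the end of December 2026, a year after follow-up is said to finish. The enrolment window, the promise of two follow-ups to each participant, the two-year timing of Visit 3 and the December 2025 end therefore cannot all be true.

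The repeat laboratory and omics measurement is what is mainly at stake. It is scheduled only at Visit 3, so a participant without Visit 3 has no within-person change in any blood marker. If the dates were followed as written, those changes would be observed only in the earliest enrollees, and whether they were observed would depend on enrolment date and on how fast each site recruited. The Statistical analysis section names last observation carried forward as one option for missing data. Because Visit 2 has no laboratory tests, carrying forward to Visit 3 would copy the baseline value and assign zero change to everyone whom the calendar excluded.

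**Working it through.** **Inputs from the article.** First enrolment 16 August 2023 (second site 22 August 2023). Enrolment ends December 2024, taken as 31 December 2024. Follow-up ends December 2025, taken as 31 December 2025. Visit 3 is at 2 years ±28 days. Target 1,000.

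**Input not in the article.** The accrual pattern. Uniform accrual is assumed first and then varied.

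**Step 1: reproduce the stated follow-up range.**
- Enrolment + 1 year: August 2023 to December 2024 becomes August 2024 to December 2025. This is exactly the stated range.
- Enrolment + 2 years: August 2025 to December 2026. This is not covered.

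So Visit 2 fits for everyone at its target date (the last is due on 31 December 2025), and Visit 3 does not.

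**Step 2: the cutoff, which needs no accrual assumption.**
- Latest enrolment with Visit 3 on its target date: 31 December 2025 − 2 years = 31 December 2023.
- Latest enrolment using the earliest edge of the window: 31 December 2023 + 28 days = 28 January 2024.

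**Step 3: the follow-up end that the visit plan needs.** The last enrollee's Visit 3 is due on 31 December 2026 ±28 days, that is 3 December 2026 to 28 January 2027.

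**Step 4: share affected under uniform accrual.** Share without Visit 3 = 1 − (days up to the cutoff / days of enrolment). Enrolment from 16 August 2023 to 31 December 2024 is 504 days, counted inclusively.

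| Cutoff | Days | Share able to have Visit 3 | Of 1,000 | Share unable |
|---|---|---|---|---|
| 31 December 2023 | 138 | 138/504 = 27.4% | 274 | 72.6% |
| 28 January 2024 | 166 | 166/504 = 32.9% | 329 | 67.1% |

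**Step 5: sensitivity of that share.**
- Other boundary dates within the stated months (start 1, 16 or 22 August 2023; enrolment end 1 or 31 December 2024; follow-up end 1 or 31 December 2025): about 63–80% unable.
- Non-uniform accrual, with cumulative share t^a of the window. Front-loaded (a = 0.5): 1 − √0.329 = 42.6% to 1 − √0.274 = 47.7%. Back-loaded (a = 2): 1 − 0.329² = 89.2% to 1 − 0.274² = 92.5%. The overall range is about 43–93%.
- If the 31 December 2025 sentence in Study procedures means the end of recruitment: about 80–88% unable.

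**Step 6: what it would take to avoid the problem.** For 80% of the cohort to be able to have Visit 3 by 31 December 2025, 80% would have to enrol in the first 166 of 504 days, which is the first third of the window.

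**Side check.** 504 days is about 16.5 months, so the label of two years in Study population does not match its own dates.

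**The case against.** The strongest reply is that the follow-up range was written for the Visit 2 round alone. It matches that round exactly, and the Study design sentence can be read the same way, with the reference to 2025 attached to the first follow-up. On that reading no participant loses Visit 3 and the text is only incomplete. This is plausible, and it is why loss of data should not be reported as certain. But Study population applies the range to all the yearly examinations, the next sentence refers to a final follow-up, and no later end date appears anywhere. The contradiction on the page stands.

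A reader might go further than the documents allow in four ways.

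- **A fixed percentage.** The 67–73% depends on uniform accrual, which the article does not state. Only the cutoff date is independent of accrual.
- **A retention target that must fail.** The article aims for retention above 80% but does not tie it to Visit 3 or define the denominator. The target would be missed at Visit 3 only if all enrolled participants are counted, including those whose visit never fell due.
- **Loss of all two-year risk estimates.** Kaplan-Meier and Cox analyses are planned. Later enrollees would still contribute first-year risk time and then be censored. Only the second-year segment would rest on early enrollees.
- **A proven second recruitment end date.** The 31 December 2025 sentence has an unclear subject. If it means the study, it agrees with the stated end of follow-up; if it means recruitment, it contradicts the December 2024 close. The two-year label may loosely mean calendar years 2023 and 2024.

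It is also fair to say that the Discussion describes phase I as a cross-sectional baseline study. Baseline blood and omics data from all participants are untouched by this point.

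**Conclusion.** The point holds as an internal contradiction of dates. With follow-up ending on 31 December 2025, participants enrolled after 28 January 2024 cannot have Visit 3 or the second blood and omics sample. That follows from the article's own dates and visit window, taking December 2025 to its last day. Assuming uniform accrual from 16 August 2023 to 31 December 2024, this is about 67–73% of 1,000, leaving about 274–329 with a possible Visit 3 before any dropout; other accrual shapes give about 43–93%.

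The consequence is limited to paired laboratory and omics change, other two-year measurements and second-year risk. If the sponsor in fact intends follow-up into 2026, the error is one of wording and no data are lost, but the article needs to say so.

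**What to change.** Reconcile Study design, the Fig 1 caption, Study population and Study procedures so that they give one set of dates, and state what the 31 December 2025 completion date refers to. There are two consistent ways to do this.

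1. **Keep two follow-ups for everyone.** State an end of follow-up that covers the last participant's Visit 3 window: to 28 January 2027 if enrolment closes on 31 December 2024. If this is not already planned, it needs a protocol and ethics-committee date amendment and roughly 12–13 more months of visits that each participant has already been promised.
2. **Keep December 2025.** State that only participants enrolled by about 28 January 2024 have Visit 3 and the second sample. Restate the expected longitudinal n from actual accrual (about 274–329 before dropout if uniform). Define the retention denominator as participants whose visit was due. Treat the others as administratively censored, and do not fill in their Visit 3 values by last observation carried forward. This costs wording and a smaller stated longitudinal sample.

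In the same edit, correct the two-year label on a window of about 16.5 months. Also reconcile the Fig 1 caption with Table 1: the caption calls Visit 3 similar in scope to Visit 2, which excludes laboratory tests, while Table 1 and Study population place laboratory tests at the final visit.

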### Study procedures

After commencing the research, banners for participant recruitment will be displayed in local public health care institutions and health centers. Contact will be initiated with individuals who respond to the banners; their age will be verified and visit schedules will be coordinated. Participants will be asked to maintain fasting for eight hours before their scheduled institution visit and to bring photographs of any nutritional supplements or medications that they are currently taking.

At the first visit, a research nurse will provide an overall explanation of the study. Then, the specific tests scheduled for the day will be detailed using a worksheet, with the nurse providing thorough explanations and addressing any queries immediately. After completing the explanations, participants will sign the research consent form and the consent form for the use of human-derived materials.

A medical registration form will be provided only to participants who sign both forms. For fasting patients, blood tests will be conducted first, and a light snack will be provided for those who complete the blood draw. Subsequently, participants will complete the all surveys and examinations. The entire examination process will take approximately 1 hour and 30 minutes. Upon completion, participants will be provided with information regarding their next examination date. Recruitment began on August 16, 2023, at Wonkwang University Korean Medicine Hospital and on August 22, 2023, at Jangheung Integrative Medical Hospital. It is expected to be completed by December 31, 2025.

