4. Health habits	Health habit about following 8 items will be measured; a. Overall wellness status b. Smoking and alcohol consumption history c. Quality of sleep d. Physical activity e. Nutritional status f. Dietary survey g. Appetite h. Social relationships	a. The Paving the Path to wellness questionnaire. b. The factor will be collected using self-report. c. Korean version of the Pittsburgh Sleep Quality Index, a subjective assessment of sleep quality over the past month, comprising 7 domains with a total of 18 questions. Scores range from 0 to 3, with higher scores indicating lower sleep quality [18]. d. The Korean Short Form of the International Physical Activity Questionnaire (IPAQ) records moderate-intensity physical activity, high-intensity physical activity, and walking performed over the past 7 days. The IPAQ score conversion guidelines are used to convert physical activity time into Metabolic Equivalent of Task (MET-min/week) scores [19]. e. The Mini Nutritional Assessment Short Form comprises 6 questions. With a total score of 14 points, a score of 12–14 indicates normal nutritional status, 8–11 suggests a risk of malnutrition, and a score of 0–7 signifies malnutrition [20]. f. To assess the overall quality of the participants’ diet, variables such as the frequency of dining out per week, companions during meals, nutritional education, and awareness of nutritional labeling are used in the dietary survey [21]. g. The Simplified Nutritional Appetite Questionnaire comprises 4 items rated on a 5-point scale, where lower scores indicate poor appetite status [22]. h. The Medical Outcomes Study-Social Support Survey is a questionnaire used to assess the nature and strength of social support among participants. It consists of a total of 19 questions rated on a 5-point scale, where higher scores indicate higher levels of social support [23].	1,2,3
5. Health service status	Accessibility of Healthcare Services	Unmet medical needs refer to the experience where individuals responded “yes” to the question, “In the past year, have there been times when you wanted to visit a hospital or clinic (excluding dental care) but could not?” This defines instances of unmet medical services (excluding dental care) as unmet medical needs [24].	1,2,3

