### Statistical analysis

We will conduct various analyses within the cohort. The results of the participants’ demographic data, the questionnaire-based prevalence of age-related symptoms and KM-based phenotype, physical function, and other outcome variables will be summarized using descriptive summary measures. For continuous outcomes, both univariate and multivariate linear regression analyses will be employed, while logistic regression will be used for dichotomous outcomes. Specifically, group differences (between KM-based phenotypes or between rural and urban areas) will be analyzed using Student’s t test and analysis of variance. The relationships between KM-based phenotypes and physical and psychological health, as well as demographic variables, will be analyzed using multiple regression.

Additionally, missing data patterns will be examined, and appropriate methods for handling missing data, such as Last Observation Carried Forward (LOCF) or Multiple Imputation, will be applied. Mixture models will be utilized to identify subgroups of subjects based on their biological and psychological characteristics. To estimate the cumulative risk of outcomes, Kaplan‒Meier analysis will be employed. Adjustments for covariates will be made before the follow-up period, during which Cox proportional hazard models will be used to estimate the risk of experiencing any of the outcomes. In addition, prediction modeling will be attempted by incorporating new covariates under investigation. P values less than 0.05 will be considered to indicate statistical significance. All statistical analyses will be conducted using SAS® version 9.4.

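### Participants are said to be selected by the areas' demographic distribution, but only banner volunteers are described; prevalence and rural-urban comparisons may therefore reflect who responds unless quotas or standardisation are used.

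*Protocol article*

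**What the plan says.** Four parts of the protocol article bear on this.

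- **Study sample.** Perfect representativeness is conceded to be out of reach. The practical answer offered is "selecting research participants based on the demographic distribution of the population aged 50–65 years in Iksan and Jangheung", as of 2023, with two population sources cited. The target population is given as "for a total of 82,498 individuals", and "the aim is to register a total of 1,000 adult participants, encompassing both sexes".
- **Study population.** Trained coordinators apply eligibility criteria on age, residence, literacy, consent, psychiatric history and medical condition. Residence covers Iksan, Jangheung and areas near each of them.
- **Study procedures.** After the study starts, "banners for participant recruitment will be displayed in local public health care institutions and health centers". Then: "Contact will be initiated with individuals who respond to the banners; their age will be verified and visit schedules will be coordinated". No other recruitment route is described.
- **Statistical analysis.** Descriptive summaries will be given of "the questionnaire-based prevalence of age-related symptoms and KM-based phenotype", among other variables. Student's t test and analysis of variance are named for group differences, including rural against urban. No covariates are attached to that comparison. Linear and logistic regression are planned more generally.

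The first aim in the Abstract and Introduction is to describe the health profiles of people entering old age in rural and urban areas.

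**The concern.** Study sample leads a reader to expect a cohort whose demographic make-up follows the two areas. Study procedures describes self-selected responders, and the eligibility criteria would not by themselves produce any particular age, sex or site distribution. Admitting residents of nearby areas also takes the eligible population beyond the one named in Study sample.

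This matters most for the first aim. A crude prevalence in volunteers mixes the age-sex composition of responders with the prevalence in each age-sex group. If that composition differs between the two sites, an unadjusted rural-urban comparison takes up the difference as well.

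The recruitment venue adds a separate problem for one outcome. Table 1 says "Unmet medical needs refer to the experience where individuals responded" yes to having wanted a hospital or clinic visit in the past year and not managed it. Banners inside health facilities are seen mainly by people who reach care, so selection into the sample may be related to this outcome directly.

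**Working it through.** **1. The plan's own figure.** Inputs from Study sample: population 82,498, about 1%, dropout 20%, target 1,000.

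- 0.01 × 82,498 = 825.
- Allowing for dropout: 825 × 1.2 = 990, or 825 / 0.8 = 1,032 (rounded up).
- In reverse: 1,000 × 0.8 = 800, and 800 / 82,498 = 0.97%.

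The target is consistent with roughly 1% retained. A sampling fraction, however, bears on sampling error and says nothing about whether the sample resembles the population.

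**2. The passages side by side.**

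| Question | Study sample | Study procedures and Study population |
|---|---|---|
| Who is chosen? | People matching the 2023 demographic distribution | Banner responders who meet the eligibility criteria |
| From where? | Iksan and Jangheung | Iksan, Jangheung and nearby areas |
| By what mechanism? | None stated | No frame, random draw or quota stated |

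**3. Possible size of an age-sex effect.** The article gives no inputs, so these are assumptions: 70% women among volunteers, 50% in the population, prevalence 40% in women and 25% in men.

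- Crude: 0.7 × 0.40 + 0.3 × 0.25 = 0.355.
- Standardised: 0.5 × 0.40 + 0.5 × 0.25 = 0.325.
- Difference: 3.0 points.
- Half-width at n = 1,000: at most 1.96 × √(0.25/1000) = 3.1 points; at p = 0.355, 1.96 × √(0.355 × 0.645/1000) = 3.0 points.
- The bias is 0.030 / 0.0151 = 1.98 standard errors, so a nominal 95% interval would cover the population value only about half the time.

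If the volunteers had the population's sex mix, this bias would be zero.

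**4. Rural-urban contrast.** Add the assumption that one site has 70% women, the other 50%, with 500 participants each (the split is not given). The same inputs then create a 3.0-point site difference where none exists. Its standard error is √(0.355 × 0.645/500 + 0.325 × 0.675/500) = 3.0 points. The spurious difference is about one standard error, which raises a nominal 5% two-sided error rate to about 17%.

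**5. What standardisation cannot do.** Suppose that, within each sex, people with the condition volunteer at r times the rate of those without. Expected prevalence in a group becomes r·p / (r·p + 1 − p). Keep the 70% share of women and the true value of 32.5%.

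| r (assumed) | Women | Men | Crude | Sex-standardised |
|---|---|---|---|---|
| 1 | 40.0% | 25.0% | 35.5% | 32.5% |
| 1.5 | 50.0% | 33.3% | 45.0% | 41.7% |
| 1/1.5 | 30.8% | 18.2% | 27.0% | 24.5% |

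Standardisation removes the sex imbalance and leaves the volunteer effect. In the last row it even moves the figure further from the truth, because the two errors had partly cancelled. Hence crude and standardised values belong side by side, with a plain label on the sample.

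**6. Cost in precision.**

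- *Sex-standardised estimate in step 3:* variance = 0.25 × 0.24/700 + 0.25 × 0.1875/300 = 0.000242, half-width 3.05 points against 2.97 crude.
- *Pooled estimate weighted by area:* with 500 per site and population shares of 70:30, 80:20 or 90:10 (neither the split nor the shares are given), the design effect is 2 × (W₁² + W₂²) = 1.16, 1.36 or 1.64. Intervals widen by about 8%, 17% or 28%.

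**The case against.** The strongest reply is that the two sections can both be true. Banners are how people are reached; demographic selection could be how they are chosen among those who respond, and coordinators are trained in recruitment procedures. A condensed article need not print quota cells. This stands in part: quotas are possible, and if applied they would remove most of the age-sex effect above. But the article mentions none, and a reader cannot tell which description governs.

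A reader might also infer more than the text supports:

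- *That prevalence will be reported unweighted.* The article says only that descriptive summaries will be used. It neither states nor excludes weighting, which may sit in a fuller document.
- *That only age is checked.* That is the first contact; the other eligibility criteria follow.
- *That the results will not describe the target population.* Neither the size nor the direction of any bias can be computed from the article.
- *That unmet need will be under-estimated.* Facility users reach care, but they may also have more need and so more occasions to answer yes. The direction is open.

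Limited representativeness is already conceded, in Study sample and in the Discussion. The first of these offers demographic selection as the remedy and the second refers to the number of participants; neither mentions self-selection or the venue. Finally, the association and marker aims are less exposed, and the planned regressions could adjust site contrasts. The tests named for those contrasts, however, carry no covariates.

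**Conclusion.** The concern holds in a limited form. The stated basis of selection is not matched by any described step, and the eligible area is wider than the population named. Unless age-sex-site quotas are applied, the prevalence summaries and the unadjusted rural-urban contrasts may partly reflect the make-up of responders. Under the assumed inputs the effect is about 3 points, comparable with sampling error at n = 1,000; with other inputs it could be nil or larger. The point bears mainly on the descriptive aim. It is a cheap improvement, not a flaw that undermines the study.

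**What to change.** 1. Reconcile Study sample with Study procedures: state the quotas by site, age band and sex, or drop the statement that participants are selected by demographic distribution. Say how residents of nearby areas fit the population named.
2. Report prevalence by site, standardised for age band and sex to the cited 2023 population, beside the crude values. This assumes those sources give counts by age and sex.
3. Adjust the rural-urban contrasts for age and sex in place of, or beside, the t test and analysis of variance.
4. Keep pooled area-weighted figures secondary, with their wider intervals shown.
5. Label the results as coming from volunteers recruited through health facilities. Note that unmet medical need may be biased by the venue in an unknown direction, and that demographic weighting does not remove this.

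The cost is a small amount of extra analysis and slightly wider intervals for the site-specific figures; the pooled ones may widen more. Age and sex are already collected, so participants need supply nothing new.
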